## Abstract

**Background:**

Healthcare workers experience higher levels of work-related stress and higher rates of sickness absence than workers in other sectors. Psychological approaches have potential in providing healthcare workers with the knowledge and skills to recognise stress and to manage stress effectively. The strongest evidence for effectiveness in reducing stress in the workplace is for stress-management courses based on cognitive behavioural therapy (CBT) principles and mindfulness-based interventions (MBIs). However, research examining effects of these interventions on sickness absence (an objective indicator of stress) and compassion for others (an indicator of patient care) is limited, as is research on brief CBT stress-management courses (which may be more widely accessible) and on MBIs adapted for workplace settings.

**Methods/design:**

This protocol is for two randomised controlled trials with participant preference between the two trials and 1:1 allocation to intervention or wait-list within the preferred choice. The first trial is examining a one-day CBT stress-management workshop and the second trial an 8-session Mindfulness-Based Cognitive Therapy for Life (MBCT-L) course, with both trials comparing intervention to wait-list. The primary outcome for both trials is stress post-intervention with secondary outcomes being sickness absence, compassion for others, depression symptoms, anxiety symptoms, wellbeing, work-related burnout, self-compassion, presenteeism, and mindfulness (MBCT-L only). Both trials aim to recruit 234 staff working in the National Health Service in the UK.

**Discussion:**

This trial will examine whether a one-day CBT stress-management workshop and an 8-session MBCT-L course are effective at reducing healthcare staff stress and other mental health outcomes compared to wait-list, and, whether these interventions are effective at reducing sickness absence and presenteeism and at enhancing wellbeing, self-compassion, mindfulness and compassion for others. Findings will help inform approaches offered to reduce healthcare staff stress and other key variables. A note of caution is that individual-level approaches should only be part of the solution to reducing healthcare staff stress within a broader focus on organisational-level interventions and support.

**Trial registration:**

ISRCTN Registry, ISRCTN11723441. Registered on 16 June 2017.

Protocol Version 1: 24 April 2017.

Trial Sponsor: Sussex Partnership NHS Foundation Trust ([contact]).

**Electronic supplementary material:**

The online version of this article (10.1186/s13063-018-2547-1) contains supplementary material, which is available to authorized users.

## Background

Healthcare workers experience disproportionately high levels of work-related stress. A recent survey in the USA found that stress was higher in healthcare workers than in any other industry, with 69% of staff reporting feeling stressed and 17% reporting high levels of stress [1]. The picture is similar elsewhere. In the UK, for example, 37% of staff working in the National Health Service (NHS) report feeling unwell due to work-related stress [30] and NHS staff are more likely to experience work-related stress compared to staff from any other public sector profession, with 61% feeling stressed all or most of the time [20]. Sickness absence is also highest in the NHS out of all the large public sector organisations [31]. In addition to the serious personal and economic consequences, high levels of stress in healthcare staff may negatively impact on patient care and safety [18]. There is therefore a need to find effective ways of reducing healthcare staff stress and interventions based on psychological theory and related psychological therapeutic interventions provide one potential solution.

It is first helpful to clarify what we mean by stress. The transactional theory of stress has arguably been most influential in recent decades [25, 26]. This suggests that stress is neither a property of situations and nor is it a property of the person. Rather, stress occurs as a transaction, or interaction between the situation and the person and arises as a consequence of the person’s appraisal of the situation. The primary appraisal concerns whether the situation is perceived as a threat to the person, and the secondary appraisal concerns whether the person perceives they have the resources (including personal resources) to cope with the threat [26]. This theory has been applied to a wide variety of contexts, including the workplace [24]. The transactional theory of stress is potentially helpful in empowering people to identify stress-related appraisals and choosing how best to respond, even in the context of highly demanding workplace situations. Cognitive behavioural therapy (CBT) and Mindfulness-Based Cognitive Therapy (MBCT) are two psychological approaches that could facilitate increased awareness of stress-related (and other) appraisals, re-evaluation or non-judgmental acceptance of these appraisals and greater awareness of choices available of how best to respond.

A meta-review found that stress-management interventions based on CBT have the strongest evidence for effectiveness in reducing work-related stress [21]. CBT stress-management involves identifying how thoughts (including appraisals), feelings, behaviours and physical sensations interact to contribute to stress, and using this information to identify strategies for preventing or reducing stress. Strategies may include identifying and re-evaluating the accuracy of stress-related thoughts (appraisals), identifying behaviours that contribute to stress and choosing alternative, more helpful behaviours, and identifying strategies to reduce physiological arousal associated with stress. By intervening in this way, the stress-related maintenance cycle between thoughts, feelings, behaviours and physical sensations can be broken and replaced with a stress-relieving maintenance cycle.

There is also growing evidence that mindfulness-based interventions (MBIs) improve stress in healthcare staff [9, 12, 14, 37, 41], including in NHS settings [28]. Mindfulness is characterised by non-judgemental awareness and acceptance of present-moment experiences (thoughts, feelings, sensations etc.), and greater awareness of helpful behavioural choices available. Mindfulness-based cognitive therapy (MBCT) [35] integrates aspects of CBT within an MBI and was originally developed to prevent depressive relapse, for which it has well-established benefits [23]. A recent adaptation for non-clinical populations that draws on the same structure and techniques as MBCT is MBCT for life (MBCT-L) [5]. Adaptations within MBCT-L include a greater focus on wellbeing, appreciation and gratitude, making this better suited in workplace settings.

In summary, there is good evidence that CBT stress-management interventions and MBIs are effective at reducing work-related stress. However, there some important gaps in the current literature.

One gap is establishing if benefits extend to reduced sickness absence. Sickness absence is estimated to cost the NHS 2.5% of its entire budget [33]. This reduces the budget available for patient care whilst placing an additional strain on staff to cover the duties of the absent member of staff, which in turn may lead to increased levels of stress and greater risk of sickness absence for staff remaining at work. Randomised controlled trial (RCT) evidence is lacking examining the potential of CBT stress-management and MBIs to reduce sickness absence.

A second gap is in investigating if the benefits of these interventions on healthcare staff stress extend to variables associated with improved patient care. There is evidence from cross-sectional studies that healthcare staff stress is associated with compromised patient safety [18], but evidence is limited as to whether interventions such as CBT stress-management and MBIs might have a causal effect on indicators of patient care such as the capacity for compassion for others. Compassion has been defined as a multi-faceted capacity involving the ability to recognise suffering, understand the universality of human suffering, feel for the person suffering, tolerate uncomfortable feelings, and the motivation to act/acting to alleviate suffering [39]. Both CBT stress-management and MBCT-L might have an effect on compassion for others (including patients) by increasing awareness of present-moment thoughts, feelings and physical reactions, cultivating understanding of human suffering as universal (as both approaches conceptualise distress using universal psychological frameworks) and increasing awareness of choices available to act to alleviate suffering.

A third gap is evidence for brief CBT stress-management interventions [21] that may be more readily accessible to healthcare staff in increasingly demanding healthcare settings. Whilst we would advocate giving sufficient time for staff to attend to their own wellbeing, we also acknowledge that many healthcare staff would struggle to attend interventions over several sessions. However, brief CBT stress-management may not be effective in comparison to their longer counterpart interventions [21] and research is needed to assess effectiveness.

Finally, a fourth gap concerns the evidence for MBCT-L. This is a newly developed intervention, designed for non-clinical settings, but we cannot assume that the benefits of MBCT for preventing depressive relapse [23] will extend to MBCT-L reducing stress in healthcare staff.

This protocol is for two RCTs examining the effectiveness of two interventions for staff working in the NHS: (1) MBCT-L and (2) CBT-based stress management. Staff will select one of these two interventions and then will be randomly assigned to either the intervention arm or to the wait-list arm within their preferred choice. Our intention in offering staff a choice between these two interventions is to increase accessibility and choice, acknowledging that no one intervention is likely to meet the needs of all staff.

Given the existing evidence for these interventions is predominantly in stress-reduction, the primary hypothesis is that both interventions will be more effective than the wait-list at reducing stress post-intervention. Secondary hypotheses are that both interventions will be more effective than the wait-list post-intervention in: (1) reducing sickness absence; (2) improving compassion for others; (3) reducing anxiety symptoms; (4) reducing depression symptoms; (5) reducing work-related burnout; (6) improving compassion for self; (7) improving wellbeing; (8) reducing presenteeism and (9) improving mindfulness (in MBCT-L participants only). We also plan to explore participants’ experiences of their chosen intervention using thematic analysis of semi-structured interviews.

## Methods/design

### Design and sample size

This protocol is for a study of two superiority RCTs with participant preference between the two interventions with 1:1 allocation to either intervention or wait-list within the preferred choice. The randomisation procedure will be web-based and automated; the allocation sequence will be generated and participants randomised using block randomisation by Qualtrics (www.qualtrics.com), the online survey software. Members of the research team involved in the day-to-day management of the study will be blind to block size. Assessments will be completed online by participants at baseline and post-intervention, independent from members of the research team, to reduce risk of bias associated with researcher-administered assessments.

Sample size calculations were conducted using G*Power [13]. The study aims to have 140 participants giving complete data sets at baseline and post-intervention within each part of the study (i.e. aiming for 140 MBCT-L and 140 CBT study completers). Given the pressures on staff time and the online data collection method, it is conservatively assumed that 40% of participants will fail to complete measures post-intervention. This means that we aim to recruit 234 participants into each part of the study.

Sample size calculations are based on an estimated medium between-group effect on post-intervention stress outcomes (Cohen’s *d* = .50) between the intervention and wait-list arms with 90% power and *p* = .05. For MBCT-L, the estimated medium effect size is based on between-group post-intervention effects on stress reported in previous trials of MBIs for healthcare staff [9, 12, 14]. For the CBT stress-management workshop it was not possible to estimate the effect directly based on published trials as previous research has evaluated CBT stress-management interventions running over several sessions. We therefore assume that the effect size will be smaller in the current study than the large effect reported in a meta-analysis of multiple-session CBT stress-management interventions in the workplace [34] and therefore estimate a medium effect size.

Ten participants from the intervention arm of each RCT, who provide complete data sets at baseline and post-intervention and who complete their allocated intervention, will be interviewed about their experiences of their intervention. The sample size for the qualitative interviews is based on recommendations for thematic analysis from Braun and Clarke [7].

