### Planned data analysis

The intention in providing two interventions is to increase choice and accessibility. The intention is not to compare the effectiveness of the CBT intervention directly with the MBCT-L intervention and any such comparison would be problematic given the potential for selection bias (i.e. participants preferring MBCT-L may differ in a number of ways from participants preferring the CBT workshop). Intervention preference will be reported as the number and percentage of participants choosing each intervention type; however we would urge caution when interpreting these data as participant preferences may be driven by practicalities (e.g. location and dates of available courses) as much as by intervention preference.

Between-group differences at baseline on key demographic variables (age, gender, ethnicity, NHS trust, pay band and years working in the trust) and all outcome measures will be reported for each study. Findings will be reported for both intention-to-treat and per-protocol analyses. Hypotheses will be tested using mixed analysis of variance (ANOVA) for each intervention separately, with time (baseline, post-intervention) as the within-group variable and intervention arm (intervention, wait-list) as the between-group variable. Post-intervention between-group effect sizes (Cohen’s *d*) and 95% confidence intervals will be reported. Interaction effects will be followed up with within-group *t* tests, with Cohen’s *d* effect sizes and accompanying 95% confidence intervals for within-group change.

Qualitative data will be transcribed and thematic analysis will be performed in accordance with the Braun and Clarke [7] protocol. This will involve the researcher leading on the qualitative aspect of the study reading and re-reading transcripts, allocating codes to single units of meaning within each transcript, identifying sub-themes representing lower-order categories of meaning across participants (within CBT/MBCT-L separately) and finally identifying higher-order themes and the relationship between themes and sub-themes (for CBT/MBCT-L separately). This will be conducted under supervision from the lead author. Credibility will be checked through supervision and will be indicated through providing comprehensive extracts from participants to illustrate each theme and sub-theme.

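### The stated 90% power with 140 completers matches a one-sided 5% test that the protocol never declares; at two-sided 5% the comparison it describes has about 84%

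*Protocol article*

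**What the plan says.** The section on design and sample size describes two superiority trials with "1:1 allocation to either intervention or wait-list within the preferred choice". It says that "The study aims to have 140 participants giving complete data sets at baseline and post-intervention within each part of the study". The calculation was done in G*Power and assumes a medium effect, a Cohen's d of 0.50 on stress after the intervention, "between the intervention and wait-list arms with 90% power and" a 5% significance level. For attrition, "it is conservatively assumed that 40% of participants will fail to complete measures post-intervention", which leads to a recruitment target of 234 per trial. The section does not say whether the 5% level is one-sided or two-sided, which G*Power procedure was used, or what correlation between baseline and post-intervention stress was assumed.

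The Background words the hypothesis directionally: "the primary hypothesis is that both interventions will be more effective than the wait-list at reducing stress post-intervention".

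The planned data analysis section says: "Hypotheses will be tested using mixed analysis of variance (ANOVA) for each intervention separately". Time (baseline, post-intervention) is the within-group factor and arm the between-group factor. Interaction effects are to be followed up, and effect sizes are to be reported with 95% confidence intervals.

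**The concern.** The sample size section gives enough detail to be checked: two equal groups, a standardised difference on the post-intervention score, a power and a significance level. A reader will take p = .05 as two-sided, since nothing says otherwise and the planned F test and 95% intervals both work at that level. On that reading 140 completers are too few for 90% power.

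What is at stake is how a null result would be read. If the stated power is taken at face value, the risk of missing an effect of d = 0.50 is believed to be 10%. For a two-sided comparison of post-intervention stress it is about 16%. The same calculation serves both trials, so both are affected.

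A second gap goes with the first. The power statement concerns a post-intervention difference between groups, while the hypothesis is to be tested in a mixed ANOVA. The time-by-arm interaction in that model is a test on change, and its power depends on a quantity that the protocol does not supply.

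**Working it through.** **Inputs from the protocol article.** d = 0.50 on post-intervention stress, power 90%, level 5% (sidedness not stated), 1:1 allocation, 140 completers (so n = 70 per arm), 40% loss, 234 recruited.

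**Method.** Two-sample t test with the noncentral t distribution: df = 2n − 2, noncentrality δ = d × √(n/2). Power is the probability that a noncentral t variable with df and δ passes the critical value (either critical value, if two-sided).

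**Step 1. Reproduce the plan's figure.** With n = 70, df = 138 and δ = 0.50 × √35 = 2.958.
- One-sided 5%: critical value 1.656, power 90.3%. With 69 per arm the power is 89.9%. So 70 per arm, 140 in total, is exactly the smallest size that reaches 90%.
- Recruitment: 140 / (1 − 0.40) = 233.3, rounded up to 234. This also reproduces.

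**Step 2. The same comparison at two-sided 5%.**
- n = 70: critical value 1.977, δ = 2.958, power 83.6% (normal approximation 84.1%). The risk of missing d = 0.50 is 100 − 83.6 = 16.4%.
- Size for 90%: 85 per arm gives 89.99% and just misses; 86 per arm gives 90.3%. That is 172 completers, and 172 / 0.60 = 286.7, so 287 recruited.
- Effect detectable with 90% power at n = 70: d of about 0.55.

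**Step 3. The planned time-by-arm test.** With two time points, the interaction in a mixed ANOVA is equivalent to a t test on the change score. Assume equal variances at both times, no true baseline difference, and a baseline-to-post correlation ρ. The change score then has standard deviation √(2(1 − ρ)) in units of the post-intervention standard deviation, so the effective standardised effect is 0.50 / √(2(1 − ρ)). The protocol gives no ρ, so the values below are assumptions. All are two-sided 5% with 70 per arm.

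| Assumed ρ | Effective d | Power |
|---|---|---|
| 0.3 | 0.423 | 70% |
| 0.4 | 0.456 | 76% |
| 0.5 | 0.500 | 84% |
| 0.59 | 0.552 | 90% |
| 0.7 | 0.645 | 97% |

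At ρ = 0.5 the divisor √(2(1 − ρ)) equals 1, so the interaction and the post-intervention comparison have the same power. Below that value the interaction is weaker, above it stronger.

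**Step 4. Baseline-adjusted analysis, for reference.** In an ANCOVA on baseline stress the effective effect is 0.50 / √(1 − ρ²). With 70 per arm, two-sided power reaches 90% at ρ of about 0.42.

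**The case against.** The strongest reply is that nothing was miscalculated. Both 140 and 234 reproduce exactly at one-sided 5%, the text never says two-sided, and the hypothesis is worded directionally. This stands in part: the defect is an undeclared and apparently one-sided level that does not match the planned analysis, and not a slip in the sums. The directional wording does not settle the matter, because superiority trials routinely word hypotheses that way and test two-sided. If one-sided 5% was intended, the F test and the 95% intervals do not follow it.

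A second reply is that the one-sided t test is only an inference about what was done. The G*Power procedure is not named, and a repeated-measures between-factors F test (f = 0.25, two measurements) also returns 140 at an assumed correlation of about 0.62 to 0.64. That is correct, but this procedure tests the arm effect averaged over baseline and post-intervention. That is neither the post-intervention effect on which the sample size rests nor the time-by-arm interaction.

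A reader might also infer that the planned analysis itself has about 84% power, or that 90% can be had only from a one-sided test. The protocol does not support either. The planned interaction has 84% power only at a correlation of 0.5, has less below that, and reaches two-sided 90% from about 0.59. Without a stated correlation no single figure can be given for it.

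Finally, the full protocol behind the article may state the sidedness. That would help, but it would not remove the mismatch between the published power statement and the published analysis if the level proved to be one-sided.

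**Conclusion.** The point holds in this form. For the comparison that the sample size section describes, 140 completers give 90% power only at one-sided 5%, and no one-sided test is declared. At two-sided 5%, the level that the planned F test and 95% intervals imply, the power is about 84%, a shortfall of some 6 percentage points. The effect detectable with 90% power is d of about 0.55 instead of 0.50. These figures rest only on the protocol's own inputs and a standard two-sample t test.

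The power of the planned time-by-arm test is undetermined. Over assumed correlations of 0.3 to 0.7 it ranges from about 70% to 97%, given equal variances and no baseline difference, so it may fall well short of 90% or exceed it. The inflation for 40% loss is correct. The statement of 90% power needs correcting, since both trials rely on it, but the recruitment target can stand.

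**What to change.** Keep 140 completers and 234 recruited per trial. State that the 5% level is two-sided, name the test behind the calculation, and restate the power, for example: *140 completers per trial give 84% power for d = 0.50 in a two-sided 5% comparison of post-intervention stress (90% for d = 0.55).*

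Add the two-sided power of the planned primary test over a stated range of assumed baseline-to-post correlations, as in the table above, with the reason for the range. If the primary test were changed to an ANCOVA adjusted for baseline stress, the same 140 completers would reach 90% at a correlation of about 0.42 or more, and the text could say so.

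The cost is a sentence or two and a slightly less favourable power statement. No extra participants are needed.
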